### Anticipated concerns

There is the potential that too few crashes will lead to non-significant results in the spatial cluster analysis since the method is pointing at spatial over-representation. This is, however, less likely to be an issue as we are using ten years of historical collision data from 4 cities and we had sufficient power to detect modest associations in our previous work (Toronto) [28].

#### Project 2C

To estimate the effect of built environment traffic features on pedestrian-MVCs and bicyclist-MVCs using a quasi-experimental design

### Study design

A quasi-experimental design will be used that will include the analysis of collision rates, pre and post traffic feature implementation.

### Location and participants

We will identify the location of newly installed (i.e., within the past ten years) traffic features in four municipalities (Montreal, Toronto, Calgary, Vancouver). Only traffic features with known implementation dates will be included in the study.

### Data collection

We will use the most recent 10-year period of police-reported traffic collision data. This project will be conducted municipality-wide, not focussed specifically on school zones as in Project 2A. Police reports of pedestrian-MVCs and bicycle-MVCs include the geographical coordinates of the collision, which will be mapped for the four municipalities. Collisions will be assigned to a feature either within a 30 m buffer-zone for point features (e.g. traffic lights) [32, 52–54] or within a 25 m buffer zone if along a roadway segment (e.g. traffic calming) [55–57]. As in other projects, potential built environment predictors will be extracted from the spatial database as described in Objective 1. The potential traffic features include (but are not limited to): 1) Traffic calming (including speed humps, chicanes, pinch points, etc.); 2) Changes in speed limits; 3) Curb extensions; 4) Traffic lights; 5) Stop signs; 6) One-way streets; 7) Level 2, uncontrolled pedestrian crossovers in residential areas; 8) Crossing guards; 9) Dead end roads; 10) Cycle lanes and cycle tracks. Location and installation dates for these built environment features will be obtained from municipality transportation departments where possible.

### Data analysis

The analysis will start with descriptive statistics of each feature and pedestrian injury rates in each municipality (Vancouver, Calgary, Toronto, Montreal). We will model collision frequency pre/post installation of each built environment feature, in each municipality, stratified on active transportation mode (pedestrian/bicyclist). The outcome will be the collision rate per feature/month (time as the offset variable). A repeated measures Poisson regression (where the feature’s site acts as its own control) will be used to model rates of pedestrian-MVCs and bicyclist-MVCs pre and post installation of the feature, controlling for feature covariates. The pre-installation period without the feature will be designated as the reference value. For features that are implemented/installed along a length of roadway (e.g., speed limits, traffic calming) we will measure collision rates using incidence density/roadway meter/month. This rate will reflect the number of collisions per meter of roadway that had the feature. For those variables that are implemented/installed at a specific point (e.g. crossing guards, crosswalks) collision rates will be measured using incidence density/traffic feature/month.

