### Anticipated concerns

It is possible that policies used by police attending incidents vary between cities. To address this concern, we will do a sub-analysis of collisions classified as serious or fatal. Research suggests more accurate reporting of serious and fatal injury by police [44–46]. It is also possible that we will not have the collision data from the same time period for each municipality. We will deal with this by basing models on the most recent years when data are available from all municipalities.

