### Anticipated concerns

It can be difficult to obtain implementation/installation dates for some traffic features [32]. We will focus on traffic features that we are able to obtain sufficient numbers with installation dates. Details of sample size and time pre and post installation will differ for each traffic feature and for each municipality; however, the feasibility of this analysis is supported by our published results from using this approach to estimate the effectiveness of pedestrian countdown signals [52], speed humps [55], school crossing guards [32], cycle lanes [56], and a streetcar right-of-way, in Toronto [57].

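### Project 2C judges traffic features by one all-severity count of police-reported collisions, so where a feature makes collisions milder the pre/post rate ratio may overstate the fall in their number

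*Protocol article*

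**What the plan says.** The data source for Project 2C is stated under its Data collection heading: "We will use the most recent 10-year period of police-reported traffic collision data". No severity restriction is given. The features listed there begin with "1) Traffic calming (including speed humps, chicanes, pinch points, etc.); 2) Changes in speed limits", followed by curb extensions, traffic lights, stop signs and others.

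The Data analysis section of Project 2C sets the comparison: "We will model collision frequency pre/post installation of each built environment feature, in each municipality, stratified on active transportation mode (pedestrian/bicyclist"). On the outcome it says "The outcome will be the collision rate per feature/month (time as the offset variable"), with a per-metre version for features along a roadway. On the model it says "A repeated measures Poisson regression (where the feature’s site acts as its own control) will be used". Severity is not mentioned there, nor in the Spatial analysis, Inter-municipality comparisons or Anticipated concerns sections of Project 2C. The last of these deals with installation dates ("It can be difficult to obtain implementation/installation dates for some traffic features"), sample size and pre/post time.

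Severity does appear in the Anticipated concerns of Project 2A. The worry there is that police policies may vary between cities. The response is "To address this concern, we will do a sub-analysis of collisions classified as serious or fatal", and the reason given is "Research suggests more accurate reporting of serious and fatal injury by police".

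**The concern.** Projects 2A and 2C draw on the same kind of police file in the same four cities. The article recognises for 2A that the quality of reporting depends on severity, but does not carry this over to 2C. In 2C the exposure may itself change severity, because traffic calming and lower speed limits act on vehicle speed.

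If collisions at a site become milder after installation, and milder collisions reach the police file less often, a smaller share of post-installation collisions is counted. The post/pre rate ratio then mixes two things: fewer collisions, and fewer collisions reported. Comparing a site with itself cancels reporting that is stable over time at that site. It does not cancel reporting that shifts because the feature has changed severity. A municipality covariate in the pooled model does not cancel it either.

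The error runs towards apparent benefit. It matters because the Inter-municipality comparisons section intends to judge which features work best in which setting, and because Objective 2 results feed the municipal toolkit of Project 3B.

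**Working it through.** Project 2C states no effect size, power or sample size, so there is no figure of the plan's own to reproduce. The check asks what the planned analysis would show if a feature changed severity only.

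**Inputs from the article:** an all-severity police-reported count, compared pre/post within site (Project 2C, Data collection and Data analysis); police reporting better for serious and fatal injury, with no rate given (Project 2A, Anticipated concerns).

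**Inputs assumed, because the article gives none:** serious share of all true collisions before (s0) and after (s1) installation; probability that a serious (rS) or minor (rM) collision is in the police file, each constant over time.

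**Formula,** with the true number of collisions held constant:

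RR = [s1·rS + (1 − s1)·rM] / [s0·rS + (1 − s0)·rM]

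Rearranged, RR = 1 − (s0 − s1)(rS − rM) / [s0·rS + (1 − s0)·rM]. The bias therefore needs both a fall in the serious share and a reporting gap. If either is zero, RR is exactly 1.

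**Results, serious share halved:**

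| Reporting serious/minor | Share 20% to 10% | Share 30% to 15% |
|---|---|---|
| 95%/70% | 0.725/0.750 = 0.97 | 0.7375/0.775 = 0.95 |
| 90%/50% | 0.540/0.580 = 0.93 | 0.560/0.620 = 0.90 |
| 95%/30% | 0.365/0.430 = 0.85 | 0.3975/0.495 = 0.80 |

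For example, at 90%/50% and 20% to 10%: before, 0.2 × 0.90 + 0.8 × 0.50 = 0.58; after, 0.1 × 0.90 + 0.9 × 0.50 = 0.54.

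**Wider grid,** rS fixed at 0.90 and the serious share halved from 10%, 20%, 30% or 40%:

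- rM 0.90: 1.00 throughout
- rM 0.70: 0.986, 0.973, 0.961, 0.949
- rM 0.50: 0.963, 0.931, 0.903, 0.879
- rM 0.30: 0.917, 0.857, 0.813, 0.778

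The spurious reduction thus runs from none, through about 1–5% and 4–12%, to 8–22%. With severity unchanged (30% before and after, 90%/50%) the ratio is 1.00.

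**What severity data would show.** In the same scenario a serious/fatal count alone gives s1/s0 = 0.50, the true change in serious collisions, provided rS is constant. The severity mix in the police file also moves: at 90%/50% and 20% to 10%, the recorded serious share goes from 0.18/0.58 = 31% to 0.09/0.54 = 17%. A before/after table would reveal the shift on which the bias depends.

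**The case against.** The strongest reply is that the article is condensed, that nothing in Project 2C is false, and that one more sub-analysis is the sort of detail left to a full plan. This has some force, but the article does set out 2C's outcome, strata, model and anticipated concerns, and it names the severity sub-analysis for the sister project. Choosing an all-severity count for a before/after evaluation of speed-related features is a visible choice, not only an unreported detail.

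Second, the 2A remark answers a different worry, namely policy differences between cities. Project 2C largely handles stable differences of that kind by modelling each city separately, using each site as its own control, and adding a municipality covariate when pooling. This stands. A reader might infer that the article contradicts itself by leaving the sub-analysis out of 2C; it does not. The 2A remark shows only that reporting is thought to depend on severity. It also speaks of accuracy, which has to be read as completeness for the bias to arise. That is the natural reading but still an inference.

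Third, nowhere does the article say that the features lower injury severity, and it gives no severity mix. The link is plausible for speed humps and speed limits, and less obvious for one-way streets, dead ends, stop signs or crossing guards. This stands too, and makes the point conditional.

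Fourth, milder injury is a real safety gain. In the scenario above the feature does help; the mistake is to describe the gain as fewer collisions. That limits the harm but does not remove it, since collision rate is the stated outcome.

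**Conclusion.** The point holds as a conditional one. If a feature makes collisions milder, and milder collisions are reported less completely, the Project 2C rate ratio may overstate the reduction in collision number, and neither own-site control nor the municipality covariate protects against this. The direction follows from the algebra. The size is unknown: about 0.95–0.97, 0.90–0.93 or 0.80–0.85 under the three assumed reporting patterns with the serious share halved from 20% or 30%, and 1.00 if reporting does not depend on severity. The ratios of 0.80–0.85 need 70% of minor collisions to go unreported.

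Two stronger readings are not supported. One is that a severity-reducing feature will appear to reduce collisions: this needs a severity shift and a reporting gap, and the documents establish neither in size. The other is that the comparison between features is distorted: this could happen if the bias differs between features, but no figure in the article shows that it does. The point is a worthwhile, cheap improvement and does not invalidate the design.

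**What to change.** Extend the serious/fatal sub-analysis of Project 2A to Project 2C:

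- Fit the same pre/post model to serious and fatal collisions, cities pooled, at least for the speed-reducing features.
- Tabulate the recorded severity mix before and after installation for each of those features.
- Where the serious share falls, report the all-severity rate ratio as possibly mixing fewer collisions with less-reported ones. The table shows whether the condition for bias is present, not how large the bias is.
- If a bias range is added, label it as resting on assumed reporting probabilities, since the police file cannot supply them.

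The cost is a little extra analysis on data that the 2A sub-analysis already presupposes are classified by severity. The drawback is imprecision: serious and fatal collisions within 25–30 m of one type of feature will be few, so intervals will be wide even with cities pooled. The serious/fatal model also answers its own question, the change in serious collisions, and supplements the all-severity ratio without correcting it.

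### Project 2C takes all pre-installation time at treated sites as its reference, so where a city installed a feature in response to recent collisions, regression to the mean may look like a safety benefit

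*Protocol article*

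**What the plan says.** The study design section of Project 2C states: "A quasi-experimental design will be used that will include the analysis of collision rates, pre and post traffic feature implementation". Sites come from a list of installations: "We will identify the location of newly installed (i.e., within the past ten years) traffic features in four municipalities". The one stated condition for entry is a known date: "Only traffic features with known implementation dates will be included in the study". Outcome data are fixed as follows: "We will use the most recent 10-year period of police-reported traffic collision data".

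The data analysis section sets the model: "A repeated measures Poisson regression (where the feature’s site acts as its own control) will be used to model rates of pedestrian-MVCs and bicyclist-MVCs". It then sets the comparator: "The pre-installation period without the feature will be designated as the reference value". No part of the time before installation is set aside, and no untreated comparison sites are described.

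Three neighbouring sections bear on the point. The spatial analysis looks at clustering and displaced traffic around treated sites. The inter-municipality section repeats the analysis over all cities with a term for municipality, in order to judge which features work best and where. The anticipated concerns cover missing installation dates and varying numbers and period lengths. None of them mentions regression to the mean.

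**The concern.** Using each site as its own control removes stable differences between sites. It does not remove a chance run of collisions that helped to bring the installation about, because that run lies inside the reference period. Rates then fall back after installation even if the feature does nothing and the city-wide rate is flat, so this is a separate problem from a time trend.

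The bias would be largest where siting responds to collisions and counts per site are low. It may therefore differ between features, and affect their ranking as well as each estimate. Project 2C aims to estimate effects, and Project 3B carries Objective 2 results into local reports and a municipal toolkit.

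**Working it through.** Project 2C gives no baseline rate, effect size or sample size, so there is no planned figure to reproduce. The calculation below shows the mechanism and its possible range.

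**Inputs, all assumed.** True rate ratio (RR) 1 and a flat background. Site rates are gamma-distributed with shape 1 and mean m child collisions per year. There are 5 years before and 5 after installation, which splits the protocol's ten-year window evenly. A share f of sites was chosen because of at least one child collision in a trigger window of W = 3 years ending at installation. The rest were sited at random.

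**Formulas for chosen sites.**
- Expected count in the trigger window: 1 + Wm
- Expected underlying rate: r = m[1 + 1/(1 + Wm)]
- RR with the full pre-period as reference: [f·5r + (1−f)·5m] / [f(2r + 1 + 3m) + (1−f)·5m]

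**m = 0.1.** The window count is 1.30 and r = 0.1 × (1 + 1/1.3) = 0.177. The pre count is 2 × 0.177 + 1.30 = 1.654 and the post count is 5 × 0.177 = 0.885.
- f = 100%: 0.885/1.654 = 0.53
- f = 50%: (0.442 + 0.250)/(0.827 + 0.250) = 0.64
- f = 20%: (0.177 + 0.400)/(0.331 + 0.400) = 0.79

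**m = 0.3.** The window count is 1.90 and r = 0.458. The pre count is 2.816 and the post count 2.289. RR is 0.94, 0.88 and 0.81 for f = 20%, 50% and 100%.

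**Other assumed rates, f = 100%.** At m = 0.05, 0.467/1.337 = 0.35. At m = 0.5, 3.5/3.9 = 0.90. Sparser counts give a larger false benefit. With random siting (f = 0), RR is 1.00 at any rate.

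**Siting on collisions at all ages.** Assume a 15% child share, so with child m = 0.1 the all-age mean is 0.1/0.15 = 0.667 per year. Choosing on at least one all-age collision in 3 years gives an all-age window count of 3, or 0.45 child collisions, and a child rate of 0.133. For f = 100%, RR = 0.667/(0.267 + 0.45) = 0.93. For f = 50% and 20% it is 0.96 and 0.98. With a trigger of at least three all-age collisions, RR is 0.95, 0.91 and 0.87 for f = 20%, 50% and 100%.

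**What leaving out a window does (m = 0.1, child trigger).**

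| Trigger years | Left out of reference | RR at f = 20% | 50% | 100% |
|---|---|---|---|---|
| last 3 of 5 | none | 0.79 | 0.64 | 0.53 |
| last 3 of 5 | last 2 | 0.87 | 0.76 | 0.67 |
| last 3 of 5 | last 3 | 1.00 | 1.00 | 1.00 |
| first 3 of 5 | none | 0.79 | 0.64 | 0.53 |
| first 3 of 5 | last 2 or 3 | 0.69 | 0.52 | 0.41 |

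Row 2 at f = 100%: the reference rate is (2 × 0.177 + 1.30/3)/3 = 0.262, and 0.177/0.262 = 0.67. Row 5: only trigger years remain, at 1.30/3 = 0.433 per year, and 0.177/0.433 = 0.41.

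**A case that no window reveals.** Suppose sites were chosen on at least one collision in all 5 pre-years. Then W = 5, the count is 1.5 and r = 0.1 × (1 + 1/1.5) = 0.167. Every pre-year has an expected rate of 1.5/5 = 0.30, so RR is 0.167/0.30 = 0.56 whichever years are dropped.

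**The case against.** A reader might infer that Project 2C will report false benefits because cities place features where collisions have occurred. The protocol does not support that. Its Background gives municipalities only a general road-safety motive, and nothing states that sites were picked on collision counts. For several listed features, such as one-way streets, dead ends or cycle lanes, a collision trigger is not obvious. This objection stands, and the point must be conditional.

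A reader might also take 0.53 as the expected size. It is near the unfavourable end of the assumptions at these rates: every site chosen, and chosen on the same child collisions that form the outcome. Nor is every unit tiny. Roadway features use a 25 m buffer along a segment and rates per metre, and segment length is not given, so counts may be higher and the bias smaller. This also stands.

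A third tempting step is to replace the primary reference with an earlier window and treat the problem as solved. The table shows otherwise. The estimate returns to 1.00 only if the omitted years cover the whole trigger period, and if the trigger came earlier the bias grows.

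Finally, this is a condensed article that cites published uses of the approach, and lead-in periods may be handled in a fuller document. That is possible. But the article does state the comparator, and the point concerns that stated choice rather than a missing detail.

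**Conclusion.** The point holds in conditional form. With treated sites only and all earlier time as reference, the RR is biased towards benefit wherever siting responded to recent collisions. The feature covariates, the displacement analysis and the municipality term do not guard against this.

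The size is unknown. For a feature with no effect and assumed child rates of 0.1 to 0.3 per site-year, RR lies between about 0.53 and 1.0. Random siting gives 1.00, and siting on at least one all-age collision gives 0.93 to 0.98 at the lower rate. Rates, trigger rule, child share and the five-year split are all assumptions. This is an inexpensive safeguard on what may be claimed, not evidence that the Project 2C results will be wrong.

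**What to change.** In the Project 2C data analysis section:

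- Keep the full pre-period estimate.
- Add a pre-specified analysis that reports collision rates by year before installation and re-estimates the pre/post RR with the last 1, 2 and 3 pre-installation years left out of the reference.
- Restrict each re-estimate to sites with enough earlier time, and give the full-period RR for the same sites so that a change of sites is not mistaken for a change of reference.
- Do not start the exclusion at the approval date. Triggering collisions come before approval, so they would stay in the reference while later, already regressed time was dropped.
- State in advance that if the estimates differ materially, or rates rise before installation, the reduction will not be attributed to the feature. State also that agreement across windows does not rule out the bias if siting used a longer collision history.

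This needs no data beyond the ten-year collision file and the installation dates already sought. The cost is wider intervals and fewer sites in the restricted analyses, because features installed early in the window have little earlier time.

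### Project 2C's pre/post model has no stated control for calendar time, so any city-wide change in collisions is absorbed into each traffic feature's rate ratio

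*Protocol article*

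**What the plan says.** All references are to Project 2C in the protocol article.

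- **Design** (Study design): "A quasi-experimental design will be used that will include the analysis of collision rates, pre and post traffic feature implementation".
- **Sites** (Location and participants): "We will identify the location of newly installed (i.e., within the past ten years) traffic features in four municipalities". Also: "Only traffic features with known implementation dates will be included in the study".
- **Data** (Data collection): "We will use the most recent 10-year period of police-reported traffic collision data". The file covers the whole municipality, not only school zones.
- **Model** (Data analysis): a repeated measures Poisson regression in which the feature's "site acts as its own control) will be used to model rates of pedestrian-MVCs and bicyclist-MVCs pre and post installation of the feature". Adjustment is for feature covariates, which are not listed.
- **Role of time** (Data analysis): "The outcome will be the collision rate per feature/month (time as the offset variable".
- **Reference level** (Data analysis): "The pre-installation period without the feature will be designated as the reference value".
- **Pooled model** (Inter-municipality comparisons): a similar analysis across cities, with municipality as a categorical covariate. It is meant to show which features work best in which setting.

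No year, season or trend term is named anywhere in Project 2C, and no comparison sites or comparison series. The Spatial analysis section looks at the broad pattern of events in each study area and at clustering around each site before and after installation. The anticipated concerns deal with missing installation dates, not with trends over time.

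**The concern.** Using a site as its own control removes differences between sites that stay fixed. It does not remove change over time. At every site the post-installation period is the later one, so the pre/post indicator also marks calendar time.

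Nothing else named in the model can separate the two. An offset only scales the count for the number of months observed. Municipality is constant within a site, so as a covariate it cannot absorb a change within that site. The denominators are feature-months or roadway-metre-months, not children, walkers, cyclists or vehicles, so a change in travel volume also passes into the rate ratio. Project 2A at least includes the proportion using active transportation as an exposure term; Project 2C names no counterpart.

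The stake is the effect estimate itself. Among the Objective 2 projects, 2C is the one whose aim is worded as estimating an effect. Its rate ratio would be the feature's effect multiplied by the background change between the two periods. A general fall in collisions would make an ineffective feature look protective, and a rise would hide a real benefit. If trends differ between cities, the cross-city comparison would read that difference as a difference in effectiveness. The results also feed the Project 3B toolkit.

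**Working it through.** Project 2C states no sample size, power or expected effect, so there is no figure of its own to reproduce. The question is what rate ratio the stated contrast returns when the feature does nothing.

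**Inputs.** From the article: a 10-year collision window, installation at some point within it, and a comparison of post with pre rates at the same site. Assumed, because the article gives no figure: a constant proportional decline d per year in collisions. The length of the pre and post periods is also not fixed; the anticipated concerns say it will differ by feature and municipality. Two cases are therefore shown.

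**Case 1: the full 10-year window at each site.** With installation at year T, the mean pre date is T/2 and the mean post date is (T + 10)/2. The gap is (T + 10)/2 − T/2 = 5 years for any T. The null rate ratio is about (1 − d)^5.

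**Case 2: two years on each side (an assumption).** The mean dates are T − 1 and T + 1, a gap of 2 years. The null rate ratio is about (1 − d)^2.

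| Assumed decline per year | Full window, (1 − d)^5 | Two years each side, (1 − d)^2 |
|---|---|---|
| 2% | 0.98^5 = 0.904 | 0.98^2 = 0.960 |
| 4% | 0.96^5 = 0.815 | 0.96^2 = 0.922 |
| 6% | 0.94^5 = 0.734 | 0.94^2 = 0.884 |

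A rise biases the other way: at +2% per year over the full window, 1.02^5 = 1.10.

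**Check of the midpoint approximation.** Averaging the declining rate over each period, instead of using midpoints, gives for d = 5% null ratios of 0.779, 0.774 and 0.769 for installation at years 2, 5 and 8. The approximation is 0.95^5 = 0.774. The installation date hardly matters when the full window is used.

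**Simulation of the model with and without a time term.** All settings are assumed: 400 sites, 120 months, installation spread over months 24 to 96, a mean baseline of 0.02 collisions per site-month, no true effect, and 300 runs for each trend. Both models condition on site.

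| Decline per year | No time term: mean rate ratio | No time term: rejected at 5% | Linear time term: mean rate ratio | Linear time term: rejected at 5% |
|---|---|---|---|---|
| 0% | 0.999 | 4% | 1.004 | 4% |
| 2% | 0.899 | 29% | 1.000 | 2% |
| 3% | 0.854 | 55% | 1.001 | 6% |
| 5% | 0.776 | 90% | 0.996 | 5% |

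The rejection rates depend on the assumed number of sites and baseline rate. The bias in the rate ratio does not. More sites would make the biased estimate more precise without moving it towards 1. Because installation dates are staggered, a calendar term can be separated from the post indicator, and adding it brings the null ratio back to about 1.

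**The case against.** **The article is condensed and does not list the feature covariates.** Year or season could be among them, or could appear in a fuller plan. This is fair up to a point: a reader might infer that the authors decided against any time adjustment, and the text does not say so. But the article does fix the eligible features, the control, the reference period and the role of time. A model built from those statements carries the trend into the effect estimate, which goes beyond an omitted detail.

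**Naming the pre-installation period as reference is correct in any such model.** This stands. The quoted sentence is not wrong in itself; the problem is that pre-installation experience at the same site is the only comparison stated.

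**The data are municipality-wide and the Spatial analysis section looks beyond the feature site.** That section does use collisions elsewhere, but its stated purposes are spatial variation and displacement of traffic. It is not linked to the rate model as a control for calendar trend. The data do make the remedy available.

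**Published Toronto analyses used this approach.** The article cites them for feasibility. Whether they adjusted for time cannot be judged from the article, so they support neither side.

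**The five-year gap is not a given.** This stands. It holds only if every site uses the full window, and the article says pre and post time will vary. Shorter windows shrink the bias, as the second case shows.

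**Regression to the mean.** A reader might infer that sites were treated after a bad run of collisions. The article does not say how sites were chosen, so this is a possibility to check and not a defect shown by the text.

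**Conclusion.** The point holds. As stated, Project 2C's model cannot tell a feature's effect from a general change in collisions, reporting or travel volume between the earlier and later months at the same site. This affects every feature in every city and the pooled comparison.

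The size is conditional. For assumed declines of 2% to 6% per year, a feature with no effect would show a rate ratio of about 0.90 to 0.73 if the full window is used, and about 0.96 to 0.88 with two years on each side. With no trend there is no bias from this source.

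It would be tempting to conclude that ineffective features will appear protective and enter the toolkit as evidence. The article does not support that. It gives no trend in either direction, and the toolkit also draws on the other projects and a three-round Delphi process. The supported conclusion is that the stated analysis leaves the effect estimate open to bias of unknown sign and size, and that data already planned can remove most of it.

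**What to change.** Keep the repeated measures Poisson model at site level and make these changes to the Project 2C analysis before it is run:

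1. Add calendar-year and month (season) terms. They are estimable where installation dates for a feature are staggered.
2. Name the concurrent comparison: sites of the same feature not yet treated, the municipality-wide collision counts already in the police file, or both. Where a feature was installed at nearly the same date throughout a city, calendar terms and the post indicator can hardly be separated, and the municipality-wide counts are then needed.
3. Report each rate ratio net of that calendar change. In the pooled model, let the calendar terms differ by municipality, so that different city trends are not read as different feature effects.
4. State the pre and post window used for each feature.

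Two optional sensitivity analyses: drop the 12 months before installation, as a limited check on possible regression to the mean, and compare with matched never-treated sites. The second costs more, because it requires confirmation that no feature was installed there, and the article itself says dates can be hard to obtain.

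The main changes need revised analysis wording and some programming, with no new collision data. Confidence intervals will be somewhat wider.
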